## Abstract

**Background::**

Diarrhea-predominant irritable bowel syndrome (IBS-D) is a kind of functional gastrointestinal disorder with obscure pathogenesis, and exploration about differential gene expression and cell heterogeneity of T lymphocytes in peripheral blood in IBS-D patients still remains unknown. Clinicians tend to use symptomatic treatment, but the efficacy is unstable and symptoms are prone to relapse. Traditional Chinese Medicine (TCM) is used frequently in IBS-D with stable and lower adverse effects. Tong-Xie-An-Chang Decoction (TXACD) has been proven to be effective in the treatment of IBS-D. However, the underlying therapeutic mechanism remains unclear. This trial aims to evaluate the clinical efficacy and safety of TXACD in IBS-D and elucidate the gene-level mechanism of IBS-D and therapeutic targets of TXACD based on single-cell sequencing technology.

**Methods/design::**

This is a randomized controlled, double-blind, double-simulation clinical trial in which 72 eligible participants with IBS-D and TCM syndrome of liver depression and spleen deficiency will be randomly allocated in the ratio of 1:1 to two groups: the experimental group and the control group. The experimental group receives Tong-Xie-An-Chang Decoction (TXACD) and Pinaverium bromide tablets placebo; the control group receives pinaverium bromide tablets and TXACD placebo. Each group will be treated for 4 weeks. The primary outcome: the rate of IBS-Symptom Severity Score (IBS-SSS). The secondary outcomes: TCM syndrome score, adequate relief and IBS-Quality of Life Questionnaire (IBS-QOL). Mechanistic outcome is the single-cell sequencing profiling of the T lymphocytes in peripheral blood from IBS-D participants before and after the treatment and healthy individuals.

**Discussion::**

This trial will prove the efficacy and safety of TXACD with high-quality evidence and provide a comprehensive perspective on the molecular mechanism of IBS-D by single-cell sequencing profiling, which makes us pinpoint specific biomarkers of IBS-D and therapeutic targets of TXACD.

## Introduction

1

Irritable bowel syndrome (IBS) is a functional bowel disorder characterized by recurrent symptoms of abdominal pain related to defecation along with altered bowel function (i.e. changes in the form or frequency of stool), which affects around 6% of the population.^[1,2]^ IBS can further be divided into four subtypes by stool consistency, namely, constipation-predominant IBS (IBS-C), diarrhea-predominant IBS (IBS-D), or a combination of both (IBS-M).^[3]^ Among them, IBS-D has the highest clinical incidence. In the absence of reliable biomarkers, diagnosis is usually based on symptom criteria. Currently, the Rome IV Diagnostic Criteria which were published in May 2016 is generally applied for diagnosis of IBS and other FGIDs.^[4]^ IBS-D negatively impacts aspects of patients’ daily activity and social wellbeing, including work productivity, social activities, and travel.^[5]^

Thus, how to effectively treat IBS-D has become an urgent medical problem to be solved. However, the onset mechanism of IBS-D remains unclear. Numerous pathological factors are involved in the occurrence and development of IBS-D, including psychological distress,^[6]^ altered gut motility, visceral hypersensitivity,^[7]^ increased gut permeability,^[8]^ abnormal regulation of brain-gut axis,^[9]^ intestinal flora imbalance,^[10]^ immune system dysfunction and low grade inflammation.^[11,12]^ Due to the heterogeneity of the pathological process, there is no specific treatment. Hence, the therapeutic effect has not been satisfactory for patients. Currently, symptomatic treatment for IBS-D is often adopted as the treatment of consensus, such as 5-HT receptor inhibitors, Intestinal motility agents, tricyclic antidepressants, probiotics and antibiotics. Among them, pinaverium bromide tablets have frequently been used to treat IBS-related abdominal pain, defecation disorder and intestinal discomfort. But many problems still remain to be solved. The efficacy of these treatments is unstable, leading to a predisposition for IBS-D symptoms to relapse.

Chinese herbal medicine, belonging to Traditional Chinese Medicine (TCM), has been traditionally used in China and other Asian countries for thousands of years and its use is now spreading worldwide. A unique and basic feature of Chinese herbal medicine is the use of a formula containing several herbs (mixed as a cocktail) to ameliorate various abnormalities related to a certain disease.^[13]^ TCM has been shown to be an effective method for treatment of IBS-D. Currently, a series of randomized controlled trials have shown that TCM can significantly alleviate the symptoms and improve the quality of life in IBS-D patients.^[14]^ Tong-Xie-An-Chang Decoction (TXACD) is composed of seven Chinese herbs, including Baizhu (Atractylodes Macrocephala Koidz), Baishao (Paeoniae Radix Alba), Huanglian (Coptidis Rhizoma), Paojiang (Rhizoma Zingiberis Preparata), Chenpi (Citrus Reticulata), Chantui (Cicadae Periostracum), Wumei (Mume Fructus). It was created by [name] from Dongfang Hospital, Beijing University of Chinese Medicine combined with his own 40 years of clinical experience, and has acquired good curative effect in the treatment of IBS-D. Previous study has shown that TXACD effectively reduced IBS-D, by relieving abdominal pain and diarrhea.^[15]^ However, TXACD therapeutic targets and molecular mechanisms directing IBS-D have not been profoundly illuminated.

About 75% of human genes can be transcribed, and transcriptome landscape is the direct reflection of encoded genetic information.^[16]^ Transcriptome profiling is able to comprehensively uncover the pathogenesis of IBS-D and the targets of TCM by analyzing the interaction networks of differentially expressed protein-coding RNAs and noncoding RNAs (ncRNAs).^[17]^ In the research of microbial ecology, cancer genome, forensic medicine, microdiagnosis, genetic imprinting and so on, the acquisition of a large number of materials has become a limiting factor for research or the data obtained from mixed materials which can’t reflect the heterogeneity of cells. Single cell sequencing solves the problem of cell heterogeneity which can’t be solved by tissue sample sequencing or when there are few samples, and provides a new direction for scientists to study and analyze the behavior, mechanism and relationship with the body of a single cell. As mentioned previously, immune system dysfunction and low grade inflammation are closely associated with the occurrence and development of IBS-D. And T lymphocytes play a key role in the pathological process. Therefore, changes in T lymphocytes transcription genes may directly affect IBS-D.

In the present trial, the primary aim of this single-center randomized controlled, double-blind, double-simulation clinical trial is to evaluate the clinical efficacy and safety of TXACD for the treatment of IBS-D, which syndrome differentiated as liver depression and spleen deficiency, and reveal the underlying mechanism of IBS-D and seek out therapeutic targets of TXACD based on single cell sequencing analysis.

## Materials and methods

2

### Ethical approval and consent to participate

2.1

The study is conducted in accordance with the Declaration of Helsinki (Edinburgh 2000 version). The final protocol (Date: 24 September 2020) of this trial has been approved by the Research Ethical Committee of Dongfang Hospital, Beijing University of Chinese Medicine (Version number: JDF-IRB2020032602). In addition, this trial has been registered in the Chinese Clinical Trial Registry (No. ChiCTR2000039357, registered on 24 October 2020). All participants will sign written informed consents before the enrollment. The patients will be fully informed of all contents of the study and details could be inquired in the registry web or the corresponding author. If there will be any significant modification of the protocol, it should be reviewed by the research ethical committee and updated on the registry web (http://www.chictr.org.cn) in time.

### Study design and recruitment

2.2

This clinical study is a single-center, randomized, double-blind, double-simulation trial comparing TXACD with pinaverium bromide tablets (PBT) in patients with IBS-D, which will be performed lasting totally 10 weeks. At the initial run-in period (weeks −2–0), we will assess eligibility and seek in-formed consent. Then, coming to the treatment period (weeks 0–4), eligible subjects will be randomly assigned to one of two groups (TXACD group and PBT group) in a 1:1 ratio and get blinded treatment of 4 weeks. Finally, we will have a follow-up (week 8) 4 weeks after the treatment. This study involves 5 site visits (week −2, week 0, week 2, week 4, and week 8) and 6 call visits (weekly call during the treatment period and follow-up). At end of this trial, the primary outcome and the secondary outcome will be evaluated. We will obtain peripheral venous blood from partial IBS-D patients (n = 8 for TXACD group) before and after treatment and recruited healthy controls group (n = 4) for the assessment of mechanistic outcome. The process of the study and visit schedule is schematically shown in Figures 1 and 2.

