### Randomization and blindness

2.4

Institute of Clinical Pharmacology of Xiyuan Hospital, China Academy of Chinese Medical Sciences was responsible for generating the allocation sequence. Random allocation method: using SAS 9.4 (SAS Institute Inc., Cary, NC) to generate random sequences, randomly grouping, and coding drugs; Concealment and implementation of allocation scheme: the secret envelope method was used to conceal the random sequences.

The double-blind trial blinded the implementers of the study (doctors) and the subjects (patients). In order to avoid the impact of blindness on other research subjects due to serious adverse conditions, only a number is given to each study object, and the medicine is distributed according to the number. Doctors and patients can only have access to the blind number in this process, and the blind bottom is kept by a person who will not participate in this study. In the event of an emergency or when the patient needs to be rescued, it is necessary to know what kind of treatment the patient is receiving, the corresponding emergency letter shall be opened in the presence of at least two researchers, and the emergency letter shall be collected together with the case report form after the end of the trial. Blind bottom leakage or emergency letter reading should not exceed 20% before the end of the trial.

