### Collection of biological specimens

2.7

The participants’ blood, stool and urine samples will be collected before and after intervention, and clearly marked in a uniform format. A designated investigator will isolate T lymphocytes single cells from the blood samples in the laboratory. Then, the isolated single cells were put into 3.5 μ l lysate and repeatedly blown with a pipette for several times, and then immediately stored at -80°C, finally transported to Shanghai OE Biotech Co., Ltd (Shanghai, China) for transcriptome sequencing.

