#### Mechanistic outcome

3.4.6

We will analyze the single-cell sequencing profiling of the T lymphocytes in peripheral blood from the TXACD granule group (n = 8) at baseline and week 4, and healthy subjects (n = 4) at baseline. In IBS-D, a complete set of transcriptional deviations enables us to search for potential molecular mechanisms and specific diagnostic biomarkers. At the same time, the therapeutic targets and pathways of TXACD in IBS-D were clarified. On the Illumina HiSeq 2000 platform, the preparation and deep sequencing of the transcriptome libraries will be performed by Shanghai OE Biotech Co., Ltd (Shanghai, China).

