#### Mechanistic data analysis

3.7.2

The differential expression analysis about mRNA for all pairwise comparisons: IBS-D patients versus healthy controls, TXACD (pre-treatment) versus TXACD (post-treatment), will be performed by Cuffdiff. An adjusted *P* < .05 (Student *t* test accompanied with Benjamini-Hochberg FDR adjustment) will be used as the cut-off point for significantly differentially expressed genes. Prediction of target genes will be performed using Pearson correlation test.

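### Only TXACD patients are sequenced, so before/after change has no randomised control and cannot be attributed to TXACD; the sections on who gives blood are also not reconciled with the blind

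*Protocol article*

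**What the plan says.** All references are to the protocol article.

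- **Who is sampled for sequencing.** Section 2.2 (Study design and recruitment): "We will obtain peripheral venous blood from partial IBS-D patients (n = 8 for TXACD group) before and after treatment", together with a "recruited healthy controls group (n = 4) for the assessment of mechanistic outcome".
- **What is sequenced, and when.** Section 3.4.6 (Mechanistic outcome): T lymphocytes "from the TXACD granule group (n = 8) at baseline and week 4, and healthy subjects (n = 4) at baseline".
- **Planned contrasts.** Section 3.7.2 (Mechanistic data analysis) lists two: "IBS-D patients versus healthy controls, TXACD (pre-treatment) versus TXACD (post-treatment), will be performed by Cuffdiff". There is no TXACD versus PBT contrast.
- **Intended conclusion.** Section 3.4.6 says that "the therapeutic targets and pathways of TXACD in IBS-D were clarified". The Discussion paragraph of the Abstract likewise promises therapeutic targets of TXACD.
- **General specimen collection.** Section 2.7 says that participants' "blood, stool and urine samples will be collected before and after intervention, and clearly marked in a uniform format", with no restriction by arm. It continues: "A designated investigator will isolate T lymphocytes single cells from the blood samples in the laboratory". The isolated cells are lysed, stored at -80°C and later shipped.
- **Blinding.** Section 2.4 blinds doctors and patients and leaves the code with a person outside the study. "Doctors and patients can only have access to the blind number in this process".

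**The concern.** There are two linked problems.

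**Attribution.** The trial has a concurrent, randomised, blinded PBT arm, but the mechanistic outcome does not use it. What remains is a before/after comparison in 8 patients who were enrolled while symptomatic (IBS-SSS above 75, section 2.3.2). Expression may change over 4 weeks through the natural course, regression to the mean, placebo response, symptom improvement from any cause, or differences in processing between time points. Healthy subjects measured once remove none of these. The main Discussion (section 4) itself notes that a placebo effect may have affected the group's earlier unblinded studies; an uncontrolled before/after contrast is open to the same doubt.

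**Sampling under the blind.** Read literally, section 2.2 defines by arm the patients who are bled for sequencing, and the first draw comes before treatment. If that were the procedure, and patients or doctors knew that only TXACD patients are chosen, being chosen would disclose the arm. Adequate relief is a self-reported yes/no answer and the primary outcome is a symptom score, so such disclosure would matter. Section 2.7 describes something different, and the two are not reconciled.

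**Working it through.** The article gives no derivation for n = 8 or n = 4, so there is no stated figure to reproduce.

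**1. What the design can estimate**

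| Group | Baseline | Week 4 |
|---|---|---|
| TXACD | 8 | 8 |
| PBT | 0 | 0 |
| Healthy | 4 | not measured |

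Write the mean change on TXACD as D + S, where D is the drug effect and S is everything else that shifts over 4 weeks. The TXACD pairs estimate only the sum. No other group is measured twice, so nothing estimates S. Adding TXACD patients sharpens D + S but does not separate its parts.

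**2. Illustrative size of the attribution error**

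Assume D = 0 and S equal to a given multiple of the SD of the change. The multiples are assumptions, since the article gives none. For a two-sided 5% paired t test on one gene with n = 8 (7 degrees of freedom), before false-discovery adjustment, the noncentrality is S × √8, and the noncentral t distribution gives:

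| S (SD of change) | Noncentrality | Probability of p < 0.05 |
|---|---|---|
| 0 | 0 | 0.05 |
| 0.5 | 1.41 | 0.23 |
| 0.8 | 2.26 | 0.50 |
| 1.0 | 2.83 | 0.68 |
| 1.5 | 4.24 | 0.95 |

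A between-arm comparison of change would stay at 0.05 in every row, provided that both arms share the shift.

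**3. Can the samples be obtained without using the code?**

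Inputs: 72 patients randomised 1:1 (sections 2.2 and 2.6), so 72/2 = 36 on TXACD. For a simple random draw of m patients made blind to arm, the number on TXACD is hypergeometric.

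- m = 8, all on TXACD: C(36,8)/C(72,8) = 30,260,340/11,969,016,345 = 0.0025.
- P(at least 8 on TXACD): m = 16, 0.611; m = 20, 0.906; m = 22, 0.964; m = 24, 0.988.

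Eight TXACD patients therefore cannot realistically be found by bleeding 8 patients blind, but they can by bleeding 22 to 24. These counts refer to patients with both samples. At the 20% loss allowed for in section 2.2, the draw would be 22/0.8 = 27.5, so 28, up to 24/0.8 = 30.

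**4. The sections side by side**

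| Section | Whose blood | Arm needed at the first draw? |
|---|---|---|
| 2.2 | some patients, 8 on TXACD | yes, if read literally |
| 2.7 | participants, no arm named | no |
| 3.4.6 | 8 TXACD patients analysed | no, if chosen later |
| 2.4 | not addressed | doctors and patients see only a number |

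Sections 2.7 and 3.4.6 together allow frozen samples to be chosen after the code is opened. Section 2.2 taken literally does not. No section says which applies.

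**The case against.** **On the blind.** A reader might infer from section 2.2 that allocation must be known before treatment, so that the blind is broken and 8 of 36 TXACD patients (22%; 8/72 = 11% of all patients) are identifiable. The documents do not support this. Section 2.7 collects participants' blood without regard to arm and freezes the cells. Section 3.5 has laboratory tests, including a blood routine test, at baseline and week 4 for participants generally, so a blood draw does not itself mark an arm. The code sits with someone outside the study, who could do the choosing. The 22% and 11% would apply only if selection were by arm, before treatment and visible to patients or doctors, and the text does not state all three. Nor does section 2.4 list the laboratory among those blinded.

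**On missing detail.** The substudy's drawing procedure is operational content that an article may leave to the full protocol, and the flow and visit figures are not shown here. Silence on that procedure is therefore not a finding. What stands is that the statements printed in sections 2.2 and 2.7 point in different directions.

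**On weight.** The mechanistic outcome is separate from the primary and secondary outcomes, so the attribution flaw leaves the randomised efficacy comparison untouched. That is correct and limits the reach of the point.

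**On sequencing both arms.** PBT is an active drug. A between-arm contrast estimates TXACD relative to PBT, and changes common to both would cancel. Splitting the 8 pairs 4 + 4 is also costly. At two-sided 5% before adjustment, 80% power needs a change of about 1.16 SD with 8 pairs but a between-arm difference of about 2.38 SD with 4 versus 4; at 1.0 SD, power falls from 0.68 to 0.22. This stands, so the split is an option and not a requirement.

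**Conclusion.** The attribution point holds on the article's own statements. With 8 TXACD pairs, no PBT pairs and healthy subjects measured once, before/after change cannot be assigned to TXACD at any sample size, yet the Abstract and section 3.4.6 claim TXACD's targets. How often this would mislead depends on the size of the shift unrelated to the drug, which the article does not give. The 23% to 68% range rests on assumed shifts of 0.5 to 1.0 SD and on single-gene tests before adjustment.

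The sampling point holds only as a conflict between sections 2.2, 2.4 and 2.7 that needs reconciling. If only TXACD patients were bled for sequencing, selection could reveal the arm; the article does not establish that this happens. No bias in the primary outcome is shown.

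**What to change.** 1. **Reconcile sections 2.2, 2.4 and 2.7.** State that baseline and week 4 sequencing blood is taken and frozen either from all participants or from a random subset drawn without regard to arm: about 22 to 24 patients with both samples, so 28 to 30 drawn if 20% are lost. State that the independent code-keeper chooses the samples to sequence after database lock.
2. **Limit the conclusion.** In the Abstract and section 3.4.6, describe the result as exploratory changes observed during TXACD treatment. Keep a claim about TXACD's effect only if PBT pairs are also sequenced and the between-arm difference in change is tested, and then word it as an effect relative to PBT. The article gives no basis for a required number of PBT pairs.

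**Cost.** Because cells are isolated and lysed before freezing, more patients than 8 must be processed at both time points, and some prepared samples will go unsequenced. The sequencing budget need not change, but the mechanistic claim becomes weaker. Adding PBT pairs to the 8 TXACD pairs would cost extra sequencing; dividing the 8 between arms would cost the power shown above.

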**Figure 1 F1:**
[figure not shown]
Flowchart of the trial. PBT = pinaverium bromide tablets, TXACD = Tong-Xie-An-Chang Decoction.

**Figure 2 F2:**
[figure not shown]
Recommended protocol items: visit schedule for enrollment, intervention, and assessments. AR = adequate relief, IBS = irritable bowel syndrome, IBS-QOL = IBS-quality of life questionnaire, IBS-SSS = IBS-symptom severity score, PBT = pinaverium bromide tablets, TCM = traditional Chinese Medicine, TXACD = Tong-Xie-An-Chang Decoction.

All 72 IBS-D patients participating in this study will be recruited from the gastroenterology department clinic or ward at Dongfang Hospital, Beijing University of Chinese Medicine. And we will additionally recruit 4 healthy controls.

According to the statistical minimum requirements for clinical efficacy evaluation of the two groups, the sample size of each group will be estimated to be 30 cases, with a total of 60 cases in both groups. After the shedding rate is calculated at 20%, the total number of cases in this study will be determined to be 72 cases.

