#### Clinical data analysis

3.7.1

Data analysis will be performed by professional statisticians and principal investigator using IBM SPSS Statistics (Version 24.0 position IBM Corp., Armonk, NY). Statistical analysis included actual number of subjects selected, cases of detachment and rejection, demographic and other baseline characteristics, patient compliance, efficacy, and safety analysis. Categorical variables will be described by frequency tables or percentages and continuous variables will be described by mean ± standard deviation. Categorical data will be analyzed by chi-square test or Fisher exact test to compare the differences between the two groups. Besides, quantitative data with normal distribution will be analyzed by T test. If the data does not conform to normal distribution or variance uniformity, Wilcoxon rank sum test or Wilcoxon signed test will be used for comparison between the two groups. A 2-sided *P* < .05 indicates statistical significance. For missing data, sensitivity analysis will be conducted and the optimal approach to the imputation of missing data will be proposed.

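### The 72 patients allow for 16.7% loss, not the stated 20%: at 20% loss about 57 to 58 remain, short of the plan's own 60

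*Protocol article*

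**What the plan says.** The sample-size paragraph stands at the end of section 2.2 of the protocol article, after the figure captions. It gives the basis as "According to the statistical minimum requirements for clinical efficacy evaluation of the two groups" and the result as "the sample size of each group will be estimated to be 30 cases, with a total of 60 cases in both groups". It then adds the loss allowance: "After the shedding rate is calculated at 20%, the total number of cases in this study will be determined to be 72 cases". The same section fixes the allocation: patients are "randomly assigned to one of two groups (TXACD group and PBT group) in a 1:1 ratio", so 72 means 36 per group. The abstract and section 2.6 (Recruitment and encouragement) repeat 72. The article nowhere defines the shedding rate in another way, for example as a share of the patients who complete.

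**The concern.** The paragraph gives a requirement (60), a loss rate (20%) and a recruitment total (72), and the three do not fit together. A loss rate is ordinarily the fraction of recruited patients who are lost, so the requirement has to be divided by one minus that rate. Multiplying by one plus the rate gives too small a total. If loss runs at the rate the plan itself expects, the trial ends below the size it calls its minimum, and a reader who takes the paragraph at face value will believe that 60 is protected.

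**Working it through.** **Inputs, all from section 2.2**
- Required: 30 per group, 60 in total.
- Shedding rate: 20%.
- Total to recruit: 72.
- Allocation: 1:1, hence 36 per group.

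**Reproducing the plan's figure**
- Requirement x (1 + rate) = 60 x 1.20 = 72. Per group, 30 x 1.20 = 36. This matches exactly.

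**What 20% loss requires**
- Requirement / (1 - rate) = 60 / 0.80 = 75.
- Per group, 30 / 0.80 = 37.5, rounded up to 38, so 76 in total with equal groups.
- The plan's 72 is 3 below 75 and 4 below 76.

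**What 72 delivers**
- At 20% loss: 72 x 0.80 = 57.6, that is 57 to 58 patients. Per group: 36 x 0.80 = 28.8, that is 28 to 29.
- Shortfall: 60 - 57.6 = 2.4 patients, and 2.4 / 60 = 4%.
- Largest loss that still leaves 60: (72 - 60) / 72 = 12/72 = 16.7%.

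**Chance of reaching the target**
Assume that each patient independently has a 20% chance of being lost. The probability that at least 60 of 72 remain is then 0.295 (binomial tail). For one group, the probability that at least 30 of 36 remain is 0.401; for both groups it is 0.401 x 0.401 = 0.16.

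**Cost in power, as a scale only**
The article states no power, so 80% and 90% are assumptions. The calculation uses a two-sided 5% level, as in section 3.7.1, and a normal approximation.
- If 30 per group gave 80%: standardised effect = (1.960 + 0.842) / sqrt(30/2) = 0.723. At 28.8 per group: 0.723 x sqrt(28.8/2) - 1.960 = 0.785, which is a power of 78.4%.
- If 30 per group gave 90%: standardised effect = (1.960 + 1.282) / sqrt(30/2) = 0.837. At 28.8 per group: 0.837 x sqrt(28.8/2) - 1.960 = 1.216, which is a power of 88.8%.

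The loss is 1.6 and 1.2 percentage points respectively.

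**The case against.** The strongest case on the other side is that this hardly matters. The gap is 2.4 patients, the power cost under either assumption is below two percentage points, and nothing in recruitment, treatment or analysis needs to change. Section 3.7.1 also foresees imputation and sensitivity analysis for missing data. If all 72 randomised patients are analysed, the shortfall concerns patients with complete data and not the number in the analysis. All of this stands, and it limits the severity. It does not make the paragraph correct, because the article states its inputs and its result, and they disagree.

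A reader might go further and infer that the trial is too small to show efficacy, particularly as the abstract says "This trial will prove the efficacy and safety of TXACD with high-quality evidence". The documents do not support that as a finding:
- A detectable difference would need a pinaverium response rate and a target power. The article gives neither, and a condensed article may leave that derivation to the full protocol or the analysis plan. Whatever the detectable difference is, the dropout slip does not cause it; it would be nearly the same at exactly 30 per group.
- The absence of a placebo-only arm is an openly stated design choice.
- The article makes no claim of non-inferiority, equivalence or comparable efficacy, so a warning about how to read a non-significant result would correct nothing in the text.
- The abstract sentence is aspirational. The aim in the Introduction is to evaluate efficacy and safety, and the closing Discussion only expresses a hope of good evidence.

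**Conclusion.** The statement is wrong as written, with minor severity. The total of 72 does not preserve 60 patients at 20% loss. It leaves 57.6, about 4% fewer than the stated minimum, and it covers a loss of 16.7%. This rests on reading the shedding rate as the share of recruited patients who are lost, which is the ordinary meaning and one that nothing in the article contradicts. The size of the gap needs no further assumption; only the binomial probabilities and the power figures do. The finding is confined to the mismatch between 60, 20% and 72. It does not extend to whether 30 per group is adequate or to what the trial can prove.

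**What to change.** Keep 72 and restate what it delivers in section 2.2, in one of two ways:
- 72 randomised patients give about 57 to 58 evaluable patients (28 to 29 per group) at 20% loss; or
- 72 randomised patients allow for 16.7% loss while retaining 60 (30 per group).

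The first keeps the expected loss rate and lowers the evaluable number; the second keeps 60 and lowers the loss that is covered. The total in the abstract and in section 2.6 stays as it is. For reference, the total consistent with both 60 and 20% is 75, or 76 with equal groups, but a gap of this size does not call for more recruitment. The cost is one sentence and a slightly less favourable stated number.
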